### Trial status

The protocol version number for this experimental design is BYL20220216. The recruitment for the experiment is scheduled to commence in December 2023, with an estimated completion date for recruitment by December 2025.

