#### Recruitment

In order to ensure the recruitment of a sufficient number of anticipated participants, our research team will collaborate with a network of 27 community health centers affiliated with Baoan People’s Hospital Group. This partnership will enable us to enlist a greater pool of potential eligible patients for inclusion in the study, and suitable participants will be selected based on predetermined inclusion and exclusion criteria. The screening logs will be maintained to document reasons for candidate exclusion. The consent process will follow the guidelines outlined in the Helsinki Declaration and the Good Clinical Practice International Coordinating Committee. Participants will receive an informed consent form that explains the study purpose, procedures, risks, and benefits and will be given adequate time to consider participation. For participants who are unable to provide their own consent, a legally authorized representative will do so on their behalf. Participants who meet the inclusion criteria and provide informed consent will be randomized to one of two groups using software-generated randomization sequences. Group allocation information will be kept confidential for the entire study period and only disclosed in special circumstances to prevent bias.

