### Study intervention

#### Randomization and blinding

This is a randomized, double-blind, controlled trial in which participants will be randomly assigned to one of two groups: the UFH group and the LMWH group. Participants will be unaware of their treatment assignment. The study aims to recruit 286 patients, with 143 patients in each group. Randomization will be conducted using a randomization sequence generated by R software. The specific method for randomization is as follows: install and load the rlist package, generate participant IDs, and use the shuffle function to randomize the participant IDs. The randomized ID data will then be arranged in order, with IDs 1–143 assigned to the UFH group and IDs 144–286 assigned to the LMWH group. Randomization will be performed by an assistant who is not involved in the study, and detailed information regarding the allocation will be kept in sealed envelopes labeled with a sequence number and will not be disclosed to participants. Data evaluation and analysis will be conducted by independent researchers under the supervision of an independent statistician. Participants, data-collecting researchers, and follow-up teams are precluded from making group allocations.

Severe adverse events include shock caused by thrombocytopenia and cerebral hemorrhage. If a severe adverse event occurs, the intervention should be discontinued if necessary, and the patient should receive appropriate rescue treatment. Blinding will be opened, and the event will be reported to the institutional review board. Compensation will be provided to subjects who are injured as a result of participating in the trial. Medical data will still be collected and analyzed. If a general adverse event occurs, patients do not need to be unblinded.

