### Confidentiality

All medical data and personal information of the participants will be kept confidential in accordance with international guidelines and regulations. Only designated members of the research team will have access to participant data, and access will be limited to the information necessary to perform their specific duties. Participant identification codes will be used instead of participant names to ensure anonymity and confidentiality. Data sharing and confidentiality agreements will be developed as needed to protect the confidentiality of research data, analytical methods used, and results obtained. Participants’ medical data and personal information will be encrypted, password protected, or stored offline as needed to ensure data security. All documents related to the study, including informed consent forms and participant medical records, will be securely stored in designated locations to ensure confidentiality.

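### Read literally, the randomization rule sets the arm by ID range after re-ordering, so the shuffle has no effect and the ID reveals the arm

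*Protocol article*

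**What the plan says.** In the Protocol article, the section Randomization and blinding sets out the method step by step. In R, the steps are to "generate participant IDs, and use the shuffle function to randomize the participant IDs". Then "The randomized ID data will then be arranged in order", and the sentence goes on: "with IDs 1–143 assigned to the UFH group and IDs 144–286 assigned to the LMWH group". The length of the list is fixed in the same section: "The study aims to recruit 286 patients, with 143 patients in each group". An assistant from outside the study carries this out, and "detailed information regarding the allocation will be kept in sealed envelopes labeled with a sequence number and will not be disclosed to participants".

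Three other sections bear on the point:

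- Recruitment: "Participants who meet the inclusion criteria and provide informed consent will be randomized to one of two groups using software-generated randomization sequences".
- Confidentiality: "Participant identification codes will be used instead of participant names to ensure anonymity and confidentiality".
- Trial status: "The recruitment for the experiment is scheduled to commence in December 2023", with completion expected by December 2025.

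The article does not say in what order patients receive IDs, or how the number on an envelope relates to an ID. The Abstract and Sample size estimation plan 456 patients, not 286.

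**The concern.** The steps as written end with an ordered list of IDs cut at its midpoint. If the ordering is by ID value, chance no longer plays any part in which ID goes to which arm, and the ID itself becomes a label for the treatment.

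Two things are at stake.

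- **Blinding.** Study design and Randomization and blinding call the trial double-blind. Baseline data are to be collected by researchers unaware of the assignment, and the brain edema score is to be read by blinded neurologists. People who never see the patient's infusion could still learn the arm from the ID on the file.
- **Validity of the comparison.** If IDs also follow the order of entry, recruiters know the next arm before they approach a patient. Any change over about two years in referral, embolization practice or imaging would then be indistinguishable from a drug effect. No analysis could separate the two, because no patient in one arm would be concurrent with a patient in the other.

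**Working it through.** **Inputs.** From Randomization and blinding: IDs 1 to 286, a shuffle, a step that puts the result in order, and a cut at 143. From Trial status: recruitment from December 2023 to December 2025. From Sample size estimation: 456 patients, and a vasospasm rate of 60% on LMWH.

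**1. The plan's own figure.** IDs 1–143 are 143 IDs and IDs 144–286 are 286 − 143 = 143 IDs, so the 143 + 143 = 286 split reproduces.

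**2. The rule run literally.** Generate 1 to 286, shuffle, sort, cut at 143. Sorting any permutation of 1 to 286 returns 1, 2, …, 286, so the outcome does not depend on the seed. Arm = UFH if ID ≤ 143, otherwise LMWH. Given the ID, the arm is known with certainty.

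**3. Three readings of the text.**

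| Reading | Next arm known in advance? | Arm tied to calendar time? | ID reveals arm? |
|---|---|---|---|
| A. Sorted list, IDs issued in order of entry | Yes | Yes, fully | Yes |
| B. Sorted list, IDs issued to patients at random | No | No | Yes |
| C. Positions in the unsorted shuffled list | No | No | No, if the ID is not the list position |

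**4. Size under reading A.**

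- There is one change of arm in 286 patients.
- Mean enrolment rank is (1 + 143)/2 = 72 for UFH and (144 + 286)/2 = 215 for LMWH.
- Correlation of arm with enrolment rank: covariance (215 − 72)/4 = 35.75. The SD of arm is 0.5, and the SD of rank is √[(286² − 1)/12] = 82.56. So |r| = 35.75/(0.5 × 82.56) = 0.87, the largest value possible for a 1:1 split.
- With even accrual (an assumption), UFH fills about the first year and LMWH about the second.

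**5. Illustration of drift under reading A.** The article gives no drift figure, so a range is assumed: a linear change of D in vasospasm risk over recruitment, centred on 60%, with no true effect. The two halves then differ by D/2. With SE = √[(p₁q₁ + p₂q₂)/143] and z = (D/2)/SE, the chance of a two-sided p < 0.05 is Φ(−1.96 + z) + Φ(−1.96 − z).

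| D | Spurious difference | Type I error |
|---|---|---|
| 5 points | 2.5 points | about 7% |
| 10 points | 5 points | about 14% |
| 20 points | 10 points | about 41% |

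For D = 10 points: SE = √[(0.575 × 0.425 + 0.625 × 0.375)/143] = 0.058, z = 0.86, and the type I error is 0.139.

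**6. Reading C for comparison.** With one shuffled block of 286, about 143 changes of arm are expected. The correlation of arm with order of entry is centred on 0, with an SD of about 0.06.

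**7. Coverage.** 456 − 286 = 170 planned patients (37%) have no assignment under the stated rule.

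**The case against.** The best defence is that reading C was intended. The article speaks of random assignment, of sequences generated by software and of envelopes with sequence numbers, and a shuffle followed by a numeric sort would serve no purpose. On that reading the main charge fails. This stands as a fair guess at intent. It does not repair the text, which ties the arm to the ID after an ordering step and never mentions list positions.

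A second defence is the safeguards: an uninvolved assistant, sealed envelopes, and randomization only after eligibility and consent. These protect a list that nobody can work out. They do not protect a rule that the article itself states, when the ID code is what stands on the patient's data. A condensed article may leave the linking of IDs and envelopes to the full protocol, and that silence is not the point here. The point is the rule that is stated.

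A reader might infer three stronger things that the documents do not support:

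- **That the next assignment is always predictable, or that UFH fills year one and LMWH year two.** Both need IDs to be issued in order of entry, which no section says. Under reading B neither holds, and only the disclosure of arm by ID remains.
- **That a single block is itself a flaw.** On reading C, the SD of the difference in arm size after 100 patients is 2√(100 × 0.25 × 186/285) = 8.1. That is an interim imbalance in numbers, not bias, and the list still ends exactly 1:1.
- **That small permuted blocks are needed.** The Abstract calls the trial open-label, so staff may know past allocations. Guessing the arm with more places left is then right about 53.5% of the time with one block of 286, against about 68% with random blocks of 4, 6 and 8. Blocking is a trade-off, not a correction.

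**Conclusion.** The concern holds for the rule as worded. Under the literal reading, arm is a deterministic function of ID, whatever the order in which IDs are issued, and that is incompatible with the stated blinding. This rests on two assumptions: that the ordering is by ID value, and that the IDs in the randomization section are the identification codes named under Confidentiality. The article describes no second code.

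Full predictability of the next patient's arm, and full confounding with calendar time, are conditional on IDs following enrolment. The drift figures in the working also rest on assumed drifts and illustrate scale only. If list positions in the unsorted shuffle were meant, the design is sound and only the wording is wrong.

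The paragraph must be corrected in either case, because a person following it as written would produce a list with no randomness in it. If that list were used in order of entry, the damage could not be undone in the analysis.

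**What to change.** Rewrite the allocation paragraph to say four things:

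1. Arm is set by the unsorted random sequence: equal numbers of the two arm labels are shuffled once with a recorded seed, and the k-th label goes into envelope k. No re-ordering follows.
2. The sequence covers the full planned sample size, with 286 and 456 reconciled throughout the article.
3. Envelopes are used in order of patient entry, and each is opened only after eligibility and consent are recorded.
4. Participant IDs carry no information on arm.

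Blocking, or stratification by WFNS grade, is optional and not needed to correct the error. If strata are added, the analysis model should include them.

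The cost is a few lines of R by the same uninvolved assistant and one rewritten paragraph, submitted to the Ethics Committee if it counts as a substantial amendment. It should be done before the first patient is randomized. If recruitment has begun, the sponsor should have someone independent of recruitment check the list actually in use and the order in which IDs were issued, and should report which of the three readings was followed.

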### Interventions, administration and duration

As part of the trial design, all enrolled patients will receive intervention following embolization of the aneurysm. The UFH group will start intravenous infusion of UFH 24 h after the embolization procedure, upon confirmation of inactive bleeding through head CT scan. The heparin will be administered at a dose of 8–10 U/kg/h, and APTT values will be monitored twice a day for 7 consecutive days. The infusion rate of heparin will be adjusted based on APTT values to maintain it within the range of 35–45 s. In case of APTT values exceeding or falling below the set range, the infusion rate will be decreased or increased by 1 IU and maintained for 12 h. As per FDA standards for the use of low molecular weight heparin, the UFH group will receive subcutaneous injection of prophylactic dose of LMWH (4000 IU) every 12 h for a duration of 1 week starting 24 h after the aneurysm repair.

All experimental UFH is stored in original packaging at 15–30 °C (protected from light and heat). LMWH is stored at 2–8 °C. After opening for more than 24 h, heparin should be discarded. During the administration process, the nursing staff is trained on medication usage and provided with dosing instructions and adverse reaction management plans for both the UFH and LMWH group. To ensure blinding, any communication between the research staff and participants that may reveal group allocation should be avoided. The identity of the medication provider should also not be disclosed.

During hospitalization, both groups of patients will be closely monitored for vital signs and symptoms in the intensive care unit. Platelet-inhibiting agents, nonsteroidal anti-inflammatory drugs, and oral anticoagulants are prohibited during the patient’s treatment period. Physicians will check for interactions with heparin when using other medications and closely monitor bleeding symptoms, adjusting the dosage of heparin or other medications as needed. All patients will receive oral nimodipine, and the blood volume will be maintained in equilibrium. The intracranial pressure of all patients will be monitored with the transducer. Transcranial Doppler (TCD) ultrasound will be performed daily to evaluate for CV, and a weekly follow-up head CT will be performed. In cases where CV or increased intracranial pressure is suspected, urgent head CT angiogram (CTA) or CT scans will be performed for confirmation.

During the use of heparin, the permissible, required, and prohibited intervention measures should comply with the inclusion and exclusion criteria. The protocol should outline all medications and treatments/interventions allowed during the study period, including emergency medications and any necessary interventions. In addition, any prohibited interventions should be included and, if necessary, a list of prohibited medications should be provided in the appendix.

We will make every effort to improve compliance with the intervention protocol, including training for nurses and other relevant researchers. The list of treatments will be used to ensure proper implementation of the intervention measures.

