### Safety assessments

To ensure the safety of the trial, it is imperative to closely monitor the patient’s condition, including changes in consciousness and vital signs. Laboratory and imaging tests are also necessary to promptly detect any adverse reactions associated with the drug, such as HIT and cerebral hemorrhage leading to cerebral herniation. Any confirmed adverse outcomes will be reported to the DSMC. In the event of a high risk of severe cerebral hemorrhage and cerebral herniation, emergency craniotomy or hematoma evacuation surgery is necessary. A decrease in platelet count is a direct manifestation of HIT. If a sharp decrease in platelet count is observed, heparin use should be immediately stopped. Common rescue drugs for severe HIT include immunoglobulin and plasma exchange.

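### The UFH titration step is printed as 1 IU, which is not a rate, and as printed one step with a 12 h hold answers any high APTT, however far above target

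*Protocol article*

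**What the plan says.** The rule is in the protocol article under Interventions, administration and duration, and concerns the UFH group only.

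- Dose: "The heparin will be administered at a dose of 8–10 U/kg/h".
- Monitoring: "APTT values will be monitored twice a day for 7 consecutive days".
- Target: "The infusion rate of heparin will be adjusted based on APTT values to maintain it within the range of 35–45 s".
- Response to any value outside that range, in either direction: "the infusion rate will be decreased or increased by 1 IU and maintained for 12 h".

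The same section says that nursing staff are "provided with dosing instructions and adverse reaction management plans for both the UFH and LMWH group"; those documents are not shown. It also has physicians check for interactions and "closely monitor bleeding symptoms, adjusting the dosage of heparin or other medications as needed". Two further provisions can stop treatment. Under Randomization and blinding: "If a severe adverse event occurs, the intervention should be discontinued if necessary". Under Safety assessments: "If a sharp decrease in platelet count is observed, heparin use should be immediately stopped".

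**The concern.** Two things in the printed rule look wrong.

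First, the step has no time unit and no weight unit. The dose is per kg and per hour, and the step changes a rate, yet it is given as a bare amount. The two obvious ways to complete it, 1 IU/h and 1 IU/kg/h, differ by a factor equal to body weight in kg.

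Second, the response does not depend on how far the APTT is from target. A value just above 45 s and a very high one get the same single step and the same 12 h hold.

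The infusion starts 24 h after embolization of a ruptured aneurysm. The Discussion describes coagulation monitoring as a common means of keeping bleeding risk in check, and that works only if the result leads to an adequate change in dose before bleeding occurs. The rule also defines the experimental treatment, so an ambiguous step makes that arm harder to deliver uniformly and to reproduce.

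**Working it through.** **Inputs.** From Interventions, administration and duration: dose 8–10 U/kg/h; APTT twice a day for 7 days; target 35–45 s; step 1 IU; hold 12 h. Assumption, not in the document: body weight 50–100 kg. U and IU are treated as the same unit. The plan prints no derived figure to reproduce, so the check is one of units and step size.

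**Number of possible adjustments.** 2 checks a day × 7 days = 14.

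**Starting rate in IU/h** = dose × weight.
- 50 kg: 8 × 50 = 400 to 10 × 50 = 500 IU/h.
- 70 kg: 560 to 700 IU/h.
- 100 kg: 800 to 1,000 IU/h.

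**Step as a share of the rate**

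| Weight | Step read as 1 IU/h | Step read as 1 IU/kg/h |
|---|---|---|
| 50 kg | 1/500 to 1/400 = 0.20–0.25% | 50/500 to 50/400 = 10–12.5% |
| 70 kg | 1/700 to 1/560 = 0.14–0.18% | 70/700 to 70/560 = 10–12.5% |
| 100 kg | 1/1,000 to 1/800 = 0.10–0.125% | 100/1,000 to 100/800 = 10–12.5% |

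On the 1 IU/h reading, 14 steps in the same direction change the rate by 14/1,000 = 1.4% at the least and 14/400 = 3.5% at the most. As a yardstick only, going from 8 to 10 U/kg/h is a change of 2/8 = 25%. A whole week of literal steps covers a small part of that.

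On the 1 IU/kg/h reading, weight cancels: 1/10 = 10% and 1/8 = 12.5%.

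**What continues after one downward step, on the likely reading**
- From 10 U/kg/h: 9/10 = 90% continues; 9 × 12 = 108 U/kg over the hold, against 10 × 12 = 120 with no change.
- From 8 U/kg/h: 7/8 = 87.5% continues; 7 × 12 = 84 U/kg, against 8 × 12 = 96 with no change.

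These amounts are the same whatever the size of the APTT excess.

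**What triggers the other printed provisions**

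| Section | Trigger | Tied to an APTT value? |
|---|---|---|
| Interventions, administration and duration (as-needed adjustment) | Drug interactions, bleeding symptoms | No |
| Randomization and blinding | Severe adverse event | No |
| Safety assessments | Sharp platelet fall | No |

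A very high APTT without bleeding, a platelet fall or an adverse event therefore falls under the single-step rule alone.

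**The case against.** The strongest reply has four parts.

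- **The unit is shorthand.** The preceding sentences give the dose in U/kg/h and the step refers to the rate, so staff would read 1 U/kg/h. That is probably right, and a reader should not infer that the trial will actually titrate by 1 IU/h. It remains a wrong unit in an operative dosing rule, not an omission, so condensation into an article does not excuse it.
- **Graded steps and critical values belong in the full protocol or the nurses' instructions.** This has force. A reader might infer that nothing in the trial deals with a very high APTT; the article does not support that, because the instructions it names are not shown. What can be said is that the printed rule covers every out-of-range value and makes no exception.
- **The 12 h hold is only the interval to the next scheduled check, and patients are in intensive care with physicians free to adjust.** The interval is indeed 24/2 = 12 h, and clinical discretion softens the point. But the as-needed clause is linked to interactions and bleeding symptoms and names no APTT level. Under Intervention discontinuation, deviations are recorded and reported, so a sensible pause could count as a departure from the printed rule.
- **No harm is quantified.** Correct. The article gives no dose-response for APTT, so neither the frequency of very high values nor any added bleeding can be estimated.

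A reader might also infer that the rule contradicts the dose range, because a patient at 8 U/kg/h has no step down, or that titration above 10 is unsafe. The contradiction arises only if 8–10 U/kg/h is a hard limit, which the text does not say. The full protocol may settle both matters.

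**Conclusion.** The point holds in two parts of unequal strength.

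The unit error is firm. It rests on the printed text alone; only the size of the literal reading, about 0.1–0.25% of the rate per step, needs the assumed weights of 50–100 kg. With at most 1.4–3.5% movement in a week, that reading could not be expected to keep APTT within 35–45 s. This is a judgement from the size of the step, since the article gives no dose-response.

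The missing override is firm as a description of the printed rule: on the 1 U/kg/h reading, 87.5–90% of the rate continues for 12 h however high the APTT is. Whether practice would follow it so literally is uncertain, because the dosing instructions are unseen and physicians have discretion. It justifies a cheap safeguard, not a claim of excess bleeding.

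No conclusion is drawn on whether 8–10 U/kg/h is a starting dose or a permitted range, or on whether a ceiling is needed.

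**What to change.** Replace the adjustment sentence with: *APTT below 35 s: increase by 1 U/kg/h. APTT above 45 s: decrease by 1 U/kg/h. Hold each step until the next 12-hourly check.* The investigators should confirm that 1 U/kg/h is what they meant.

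Add one sentence: *An APTT above the threshold set by the investigators and DSMC before the first patient overrides the hold: pause the infusion, recheck the APTT early, and restart at a lower rate.* The threshold, recheck time and restart rate are theirs to choose; the article gives no values. If the nurses' dosing instructions already contain such a limit, cite it here.

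Make those instructions match the text. The cost is a few sentences and an occasional extra APTT. The change should be in place before the first patient, with recruitment planned from December 2023 under Trial status.

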## Abstract

**Background:**

Heparin anticoagulation therapy is a widely used method to prevent cerebral vasospasm (CV) and venous thrombosis in patients with subarachnoid hemorrhage caused by ruptured cerebral aneurysms. Subcutaneous heparin injection is considered safe and effective, whereas continuous intravenous heparin infusion is still being debated due to the risk of bleeding. Although most retrospective studies have confirmed the safety and effectiveness of unfractionated heparin (UFH) after aneurysm embolization therapy and its ability to reduce CV, there is still no randomized clinical trial comparing UFH and subcutaneous low-molecular-weight heparin (LMWH) injection in this population. Therefore, this study aims to compare the clinical outcomes associated with these two treatment approaches.

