In patients undergoing endovascular treatment for aSAH, continuous maintenance of arterial catheters with UFH during surgery contributes to the reduction of thrombus formation, while subcutaneous injections of low-molecular-weight heparin (LMWH) prevent formation of lower-extremity deep veinous thrombosis. However, both LMWH and UFH infusions have their pros and cons. Although neurocritical care guidelines recommend initiating subcutaneous heparin 24 h after aneurysm embolization surgery [9], the UFH injection has limitations due to its high molecular weight and low bioavailability. Intravenous UFH may, therefore, be considered more reliable.

Research indicates that low-dose intravenous UFH infusion yields favorable outcomes in reducing CV and ischemic complications. Multiple retrospective studies have demonstrated the safety and efficacy of low-dose continuous intravenous UFH infusion. However, there is controversy regarding the optimal dosage and duration of treatment. A retrospective study by J. Marc Simard revealed the safety of low-dose (8–9 U/kg/h) intravenous UFH administration in aSAH patients, without any cases of bleeding, heparin-induced thrombocytopenia (HIT), or deep vein thrombosis, and the incidence of clinical vasospasm significantly decreased compared to subcutaneous LMWH usage [10]. Another research by Markus Bruder in endovascular treatment for aSAH patients showed a lower probability of cerebral infarction when combining UFH with LMWH [11].

Regarding the timing of initiating of heparin, Annika’s study suggested that using heparin within 24 h after aneurysm repair might be safer and carry a lower risk of bleeding compared to initiating treatment 48 h later [12]. Randomized controlled trial results comparing subcutaneous injections of LMWH and intravenous infusion of UFH are currently lacking, although randomized controlled studies have shown the safe and effective reduction of CV and ischemia with subcutaneous injection of enoxaparin compared to placebo in patients with aSAH [13].

This study is a single-center exploratory randomized controlled trial comparing the impact of low-dose intravenous infusion of UFH and subcutaneous injection of LMWH on the incidence of CV in aSAH patients. The outcomes to be assessed also include the occurrence of bleeding events, ischemic events, HIT, deep vein thrombosis, cerebral venous circulation time, brain edema score, and hydrocephalus incidence.

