### Sample size estimation

The primary outcome of this study was the incidence of CV. J. Marc’s research indicated that the incidence of CV was 58% and 60% in the groups receiving intravenous unfractionated heparin and subcutaneous low molecular weight heparin, respectively [10]. The hypothesis was that the unfractionated heparin protocol was superior to the subcutaneous low molecular weight heparin injection in reducing the incidence of CV. The sample size of the study was calculated using a bilateral test to achieve a target effect of 0.1 and an α error of 0.05. Considering a dropout rate of 10%, each group would require 228 patients, so a total of 456 participants will be enrolled. The sample size was estimated using PASS (version 15.0.3, NCSS, LLC, Kaysville, Utah, USA).

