UFH accelerates the inactivation of factors Xa and IIa by binding to thrombomodulin III, preventing the obstruction of blood flow by thrombin, and reducing the risk of thrombus formation [8]. LMWH also acts by enhancing the inhibitory activity of antithrombin III (ATIII) on factor Xa, preventing thrombin formation, and reducing the risk of clot [27]. Thrombophilia can induce platelet activation and aggregation, as well as the release of thromboxane A2 and serotonin, which promote vasoconstriction and contribute to CV. Clots can also mediate the release of inflammatory mediators, causing endothelial dysfunction and an imbalance between vasoconstrictive and vasodilatory factors, which can also result in vasospasm. In summary, heparin indirectly inhibits the occurrence of CV by reducing thrombus formation through ATIII.

The choice between LMWH and UFH depends on balancing the antithrombotic effect and bleeding risk. Some non-randomized clinical trials have demonstrated that heparin can reduce the occurrence of ischemia in aSAH. The beneficial effects of heparin are influenced by the type of heparin and the duration of administration. However, there is no significant difference in the incidence of CV-related to LMWH and UFH, suggesting the possibility that heparin may exert beneficial effects through mechanisms other than preventing CV. The impact of heparin on cerebral edema and cerebral venous circulation in aSAH has not been studied.

This randomized trial aims to compare the safety and efficacy of UFH and LMWH in aSAH and analyze their effects on CV, brain edema, and cerebral venous circulation.

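### The dosing text gives both the intravenous UFH and the subcutaneous LMWH to the UFH group and states no regimen for the LMWH group

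*Protocol article*

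**What the plan says.** The section headed Interventions, administration and duration contains two regimens.

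- The first: "The UFH group will start intravenous infusion of UFH", beginning 24 h after embolization once CT shows no active bleeding, at 8–10 U/kg/h. APTT is checked twice daily for 7 days and the rate is adjusted to keep it at 35–45 s.
- The second opens by referring to FDA standards for LMWH and then states that "the UFH group will receive subcutaneous injection of prophylactic dose of LMWH": 4000 IU every 12 h for 1 week, from 24 h after aneurysm repair.

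Both sentences name the UFH group. The LMWH group appears later in the section, where nurses are to be given "dosing instructions and adverse reaction management plans for both the UFH and LMWH group", but the content of those instructions is not set out.

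Elsewhere the article describes a comparison of two agents. Under Randomization and blinding, "participants will be randomly assigned to one of two groups: the UFH group and the LMWH group". The Background describes a trial "comparing the impact of low-dose intravenous infusion of UFH and subcutaneous injection of LMWH on the incidence of CV". The hypothesis under Sample size estimation is that "the unfractionated heparin protocol was superior to the subcutaneous low molecular weight heparin injection in reducing the incidence of CV".

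**The concern.** The two dosing sentences cannot stand beside the stated design. If they are right, one arm receives two heparins together and the other has no written schedule. If the design statements are right, the second dosing sentence names the wrong arm.

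Two things are at stake. The first is safety. This is anticoagulant dosing beginning 24 h after repair of a ruptured intracranial aneurysm, in a trial that counts bleeding among its secondary outcomes and names cerebral hemorrhage as a severe adverse event. The second is what the trial estimates. With LMWH in the UFH arm, the difference in vasospasm would no longer be intravenous UFH against subcutaneous LMWH. If the other arm also received LMWH, it would be the effect of adding UFH. If the other arm received something else, the contrast could not be named from the text.

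**Working it through.** The plan gives no statistical figure to reproduce on this point. The check sets the statements side by side and then sizes the literal reading.

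**Step 1: regimens by arm in the available text**

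| Arm | Intravenous UFH | Subcutaneous LMWH |
|---|---|---|
| UFH group | 8–10 U/kg/h from 24 h, APTT-adjusted | 4000 IU every 12 h, 1 week, from 24 h |
| LMWH group | none stated | no dose, frequency, start or duration stated |

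The drug and route for the LMWH group can be inferred from the group's name and from the abstract, background and sample size section. The schedule cannot, except by moving the second regimen across.

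**Step 2: what the rest of the article requires**

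- Abstract: the gap to be filled is the lack of a randomized trial "comparing UFH and subcutaneous low-molecular-weight heparin (LMWH) injection in this population".
- Background: intravenous UFH against subcutaneous LMWH.
- Randomization and blinding: two groups, each named for one agent.
- Sample size estimation: UFH superior to subcutaneous LMWH, with planning rates of 58% and 60% attributed to intravenous UFH and subcutaneous LMWH respectively.
- Discussion: "This randomized trial aims to compare the safety and efficacy of UFH and LMWH in aSAH".

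No statement of the design describes a combined UFH-plus-LMWH arm.

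**Step 3: which reading is likelier**

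The second dosing sentence starts from standards for LMWH and gives its own start time and duration, as the description of a second arm would. The section also says that every enrolled patient receives an intervention, and it refers to dosing instructions for both groups. Replacing UFH group with LMWH group in that sentence gives each arm one regimen and agrees with every item in Step 2. A slip is therefore the likeliest reading.

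**Step 4: size of the literal reading**

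Inputs are the doses in the section on interventions, administration and duration.

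- LMWH: 24 h / 12 h = 2 injections per day; 2 × 4000 IU = 8000 IU/day; 2 × 7 = 14 injections; 14 × 4000 IU = 56,000 IU over the week.
- UFH at the starting rate: 8 × 24 = 192 U/kg/day and 10 × 24 = 240 U/kg/day.
- Body weight is not given. At an assumed 70 kg, UFH would be 70 × 192 = 13,440 to 70 × 240 = 16,800 U/day. Over an assumed 50–90 kg the range is 50 × 192 = 9,600 to 90 × 240 = 21,600 U/day.

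The rate is later adjusted to APTT, so these are starting rates and not fixed totals. The two drugs' units are kept apart and not added. The arm left without a written schedule has 228 patients by the sample size section, or 143 by the randomization section; that discrepancy is a separate matter.

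**The case against.** The strongest reply is that this is an editorial slip which a careful reader resolves. There are two named arms and only one LMWH regimen, so it is clear where the regimen belongs. The document is also a journal article. The flowchart and the schedule table are not visible here, a full protocol is said to be available on request, and nurses are to work from separate dosing instructions and a treatment list. Nothing shown says that anyone doses patients from this sentence, and the cumulative doses above describe a reading that is itself thought unlikely.

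Much of this stands. The error is probably one word, the LMWH arm's drug and route are not in doubt, and it cannot be seen whether the working documents repeat the mistake. The dose figures show what following the sentence would mean; they do not predict what will happen.

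The objection does not remove the error. Condensing a protocol explains omissions, but this is a positive statement that assigns a drug to an arm, and nothing in the article corrects it. Nor is the combination excluded as an intention. The Background cites a study reporting fewer cerebral infarctions when UFH and LMWH were combined, the hypothesis refers to a UFH protocol without defining it, and the prohibited drugs listed in the interventions section (platelet inhibitors, NSAIDs and oral anticoagulants) do not include a second parenteral heparin. A reader could take the sentence at face value.

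**Conclusion.** The concern holds. The dosing section is wrong as written or, less probably, describes a combination arm that the rest of the article does not declare. Two regimens are assigned to the UFH group and none to the LMWH group, in conflict with the aim, the randomization and the hypothesis. It must be corrected because it determines which anticoagulant each arm receives, even though the cause is probably a single word.

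The conclusion rests on the available text only. The schedule table, flowchart, full protocol and nursing instructions may be correct; if so, the printed sentence conflicts with them and still needs changing.

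**What to change.** 1. Confirm with the investigators what each arm is to receive.
2. If it is a slip, change the second mention of the UFH group in the dosing paragraph to the LMWH group. Check that the full protocol, the schedule table and the nursing instructions agree. The cost is a one-word correction, notification of the ethics committee and that check. The design does not change.
3. If LMWH is meant to be given with UFH, or in both arms, state each arm's products, doses, start times and durations. Restate the aim and the hypothesis to match. Replace or justify the 58% and 60% planning rates, which are attributed to intravenous UFH and subcutaneous LMWH as separate regimens, and recheck the sample size. This is a substantive amendment.
4. A minor wording point in the same paragraph: the titration step is given as 1 IU while the infusion is dosed in U/kg/h. State the step in the unit of the infusion, presumably 1 IU/kg/h.
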